### Missing data

When determining the sample size for the examination, the potential for participants to become untraceable is considered and factored into the calculations. Furthermore, any missing data (such as loss to follow-up, death, withdrawal, etc.) will be addressed using the multiple imputations approach to ensure completeness.

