**Method and design:**

This study is designed as a randomized controlled trial. A total of 26 class III skeletal patients with maxillofacial abnormalities will be recruited from the maxillofacial clinic of Bu-Ali and Farahikhtegan Hospitals in Tehran, Iran. Patients meeting the inclusion criteria will be randomly assigned to two groups: one group will undergo LeFort I osteotomy with ANS reduction, and the other group will undergo LeFort I osteotomy without ANS reduction. The soft tissue profile changes, specifically the nasolabial angle and upper lip length, will be evaluated and compared between the two groups.

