## Methods

### Overview

This research is planned as a randomized controlled trial. The goal is to enroll 26 class III skeletal patients from the patients who refer to the maxillofacial clinic of Bu-Ali and Farahikhtegan Hospitals in Tehran, Iran, who suffer from maxillofacial abnormalities. We will have 2 groups: (1) control group (without ANS reduction) and (2) intervention group (with ANS reduction). This project was registered at The Iranian Registry of Clinical Trials (Identifier No. IRCT20210928052625N1, Website: https://www.irct.ir/trial/59171) and Open Science Framework (OSF) (Registration 10.17605/OSF.IO/X3HD4). Recruiting and treatment methodology of this study is confirmed by the Research Ethics Committee of the Islamic Azad University Dental Branch, Tehran, Iran (IR.IAU.DENTAL.REC.1400.035). Each participant’s overall health will be assessed by researchers before creating a treatment plan (Fig. 1 and Table 1).

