### Sample size

According to the results of the study by Mahsoub R, et al., using the Advanced Repeated Measures Anova Power Analysis option of the Pass11 software, considering *α* and *β* = 0.05 for both within-between subject variables equal to 0.2, the repeated factor with two repetitions and the effect size equal to 0.5 and the two-way between subject factor with an effect size equal to 0.6, the minimum sample size required for each of the two study groups was calculated as 13 samples [16].

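### Missing data says loss to follow-up is built into the sample size, but no stated figure shows an allowance: the enrolment target of 26 is exactly twice the calculated minimum of 13 per group

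*Protocol article*

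**What the plan says.** Three parts of the protocol article bear on this.

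- **Missing data** says of the sample-size determination that "the potential for participants to become untraceable is considered and factored into the calculations". It gives no rate. It then names loss to follow-up, death and withdrawal as sources of missing data, to be handled by multiple imputation.
- **Sample size** describes a calculation made "using the Advanced Repeated Measures Anova Power Analysis option of the Pass11 software". The inputs are α and β ("0.05 for both within-between subject variables equal to 0.2", a garbled phrase most naturally read as α = 0.05 and β = 0.2), an effect of 0.5 for the within-patient comparison over two time points, and an effect of 0.6 for the comparison between the groups. The result is that "the minimum sample size required for each of the two study groups was calculated as 13 samples".
- **Enrolment target.** The Abstract says "A total of 26 class III skeletal patients with maxillofacial abnormalities will be recruited", and the Overview says "The goal is to enroll 26 class III skeletal patients". The Discussion also speaks of twenty-six patients.

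The Intervention section adds that patients leave the trial if they become pregnant, abandon their orthodontic treatment or withdraw. The outcome needs a second cephalogram three months after surgery.

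**The concern.** An article may leave the dropout rate to a fuller document, and its absence alone would be no finding. Here the article makes a positive claim, that losses were allowed for, and the figures printed beside it show nothing added. The inputs include no loss rate, the output is called a minimum, and the target is that minimum doubled.

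The reader's ability to judge the result is at stake. The trial is small and its hypothesis is stated as no difference. If it ends with a null result and some patients missing, a reader who trusts the Missing data sentence will assume that the planned power survived the losses. Nothing printed supports that assumption. Multiple imputation does not fill the gap, because imputing an outcome does not restore the information lost with it.

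**Working it through.** **1. Implied inflation.** Inputs: 13 per group (Sample size), two groups, 26 enrolled (Abstract, Overview).

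26 / (2 × 13) = 1.00, so the visible allowance is 0%.

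**2. Can the 13 be reproduced without an allowance?** Assume α = 0.05 two-sided, power 0.80, and effect sizes read as Cohen's f. For the between-group factor with f = 0.6 and one value per patient, power comes from the noncentral F with 1 and N − 2 degrees of freedom and λ = N·f².

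| Per group | N | λ = N × 0.36 | Power |
|---|---|---|---|
| 13 | 26 | 9.36 | 83.5% |
| 12 | 24 | 8.64 | 80.2% |
| 11 | 22 | 7.92 | 76.3% |
| 10 | 20 | 7.20 | 71.8% |

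This equals a two-sample test at d = 2f = 1.2. The bare minimum for 80% is 12, so 13 is reproduced to within one patient per group.

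**3. How far this depends on the model.** The plan used a repeated-measures model, and the article does not give the within-subject correlation ρ. If the group comparison averages the two measurements, λ = N·f²·2/(1 + ρ). The number needed per group is then 7 (ρ = 0), 10 (ρ = 0.5), 11 (ρ = 0.7 to 0.8) or 12 (ρ = 0.9 to 1). Power with 10 per group runs from 71.8% (ρ = 1, λ = 7.20) to about 95% (ρ = 0, λ = 14.40). For the within-subject factor with f = 0.5, the number is 17 per group under λ = N·f², or 6 to 9 under λ = 2N·f²/(1 − ρ) with ρ from 0.5 down to 0. The exact PASS result cannot be recovered from the article, and the table in step 2 is one conditional reading.

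**4. What an allowance on top of 13 would look like.** No rate is given, so a range is assumed, using n / (1 − loss), rounded up per group:

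| Assumed loss | 13 / (1 − loss) | Per group | Total |
|---|---|---|---|
| 5% | 13.7 | 14 | 28 |
| 10% | 14.4 | 15 | 30 |
| 15% | 15.3 | 16 | 32 |
| 20% | 16.25 | 17 | 34 |

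None of these totals is 26.

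**5. Could 13 already contain an allowance?** Numerically, yes. From a bare 12, 12/0.95 = 12.6, which rounds up to 13, and any loss up to 1 − 12/13 = 7.7% gives the same. From a bare 11, 11/0.90 = 12.2 and 11/0.85 = 12.9, both rounding up to 13. The article states neither a bare number nor a rate.

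**The case against.** The strongest reply is that 13 may be an inflated figure. On the simple between-group reading 12 per group already reaches 80%, so 13 could be 12 plus a small allowance, and Missing data would then be true. This stands as a possibility, and for that reason one cannot infer that the allowance does not exist or that the sentence is false. The text gives it no support, however. Sample size presents 13 as the software's result and as the minimum required, from inputs without a loss rate.

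A reader might also infer that any dropout takes the trial below its planned power. The documents do not support that. Any loss takes a group below the stated head count of 13, which is a different matter. On the two-sample reading one loss in each arm leaves 80.2%, and with averaged, imperfectly correlated measurements power is higher still.

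It is also fair to say that the two-sample test is not the plan's model, so its power figures should not be written into the protocol as fact, and that the article lists reasons for leaving without predicting how often they occur. Both points stand. Neither reconciles the two sections.

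**Conclusion.** The point holds as an inconsistency between Missing data on one side and Sample size with the enrolment target on the other. The article claims an allowance for loss that appears in none of its figures; the visible inflation is 0%. This part rests only on printed numbers and needs no power model.

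The effect on power is less certain. If f = 0.6 is read as d = 1.2 in a two-sample test, power falls from 83.5% with 26 completers to 80.2%, 76.3% and 71.8% with 24, 22 and 20, losses being equal in the two arms. These figures assume α = 0.05 two-sided and one value per patient, and under the averaged repeated-measures reading they are lower bounds. A modest loss need not bring power below 80%. The enrolment target itself is not shown to be wrong.

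**What to change.** Keep 26 and reconcile the two sections according to what was actually done.

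- **If no loss rate was used:** delete the sentence in Missing data. State in Sample size that 13 per group is the uninflated number of completers and that 26 includes no allowance for loss. Restate power for fewer completers (for example 24, 22 and 20) from the same PASS repeated-measures model, giving its within-subject correlation. Do not substitute the two-sample figures above.
- **If a loss rate was used:** state the rate and the uninflated number per group, and show the step from that number to 13.

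The cost is a few sentences and, in the first case, a rerun of the existing power calculation. Recruitment, randomisation, outcomes and analysis are untouched. The only consequence is that the stated protection against loss may read less favourably.

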## Ethical consideration

### Ethical approval

The recruitment and treatment procedures for this study were approved by the Research Ethics Committees, Islamic Azad University-Dental Branch, Tehran, Iran (IR.IAU.DENTAL.REC.1400.035). Eligible participants will receive detailed information about the trial’s consent requirements. Individuals who do not provide consent will not be included in the final analysis.

### Withdrawal

All patients will be given all the information they need about the study before any treatment begins. Patients can leave the study at any time for any reason. All patients will receive the best care possible, whether or not they participate in the study.

### Publication of results

The results of the study will be published in a scientific journal, and the analysis will be posted online for everyone to see.

## Oversight

### Trial management

The current clinical study is being led by the Oral and Maxillofacial Department, Dental Faculty, Tehran Medical Sciences, Islamic Azad University, Tehran, Iran. The research team will receive support and assistance from this coordinating center in various aspects of the study, such as trial design, quality assurance, data analysis, dissemination, and study management.

### Steering committee

The trial steering group consists of multiple patients, public representatives, two independent doctors, and a statistical expert who have been recruited to provide guidance and oversight throughout the study. The committee members will convene with the study group every 2 months and will not be directly involved in the operational aspects of the trial. Their responsibilities include offering recommendations to the research team regarding the trial’s implementation, data management, monitoring, recruitment, and follow-up methods. They will also be responsible for analyzing the results and tracking the progress of the trial to make sure it is being done according to the plan.

### Data monitoring

The trial’s advancement, any adverse events, and data quality will be overseen by an independent data monitoring committee (DMC). This committee consists of members from the Ethics Committee of the Dental Faculty, Tehran Medical Sciences, Islamic Azad University, Tehran, Iran, who are not associated with the trial investigators, research team, or sponsors. The research team will regularly meet with an auditor appointed by the DMC every 2 months to monitor the study’s progress and conduct an initial analysis. The DMC has the authority to halt the trial if any injuries or risks are identified based on interim findings.

### Harms

There will be no significant injury to research participants, and the surgery method has a minimal probability of failure. The same surgeon will do all of the operations. To reduce the danger of injury, all required precautions will be followed. If something goes wrong, the participants will have a backup restoration plan in place. If a surgical failure occurs together with unanticipated side effects or major adverse events, the DMC will be notified very once.

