### Training and calibration

The surgical process will be performed by one specialist ([name]) with over 15 years of professional working experience. He is also an expert in the field of orthognathic surgery. An independent investigator will do the measurements before the surgery and after that. The research team consists of an oral and maxillofacial surgery resident and a final-year dental student, both of whom have a minimum of 4 years of clinical experience and have received training in accuracy and reproducibility to ensure compliance. A certified researcher with extensive years of expertise will be responsible for collecting clinical data, patient testimonials, and information on complications to maintain consistency.

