## Challenges and limitations

One of the challenges that may occur during the LeFort I osteotomy is the incidence of hematoma and edema. Nasofrontal angle may change due to errors during surgery. It is also possible to create a depression in the sub-nasal area due to excessive removal of the ANS.

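### The one explicit rule for notifying the DMC requires a surgical failure and an adverse event together, which is narrower than the DMC's stated remit

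*Protocol article*

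**What the plan says.** Five sections of the protocol article bear on this.

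- **Harms** opens with an assurance: "There will be no significant injury to research participants, and the surgery method has a minimal probability of failure". It ends with the notification rule: "If a surgical failure occurs together with unanticipated side effects or major adverse events, the DMC will be notified". The timing words that follow are garbled, but they seem to mean prompt notice.
- **Data monitoring** sets the DMC's remit without mentioning surgical failure: "any adverse events, and data quality will be overseen by an independent data monitoring committee (DMC". The research team meets a DMC-appointed auditor every 2 months. The section closes: "The DMC has the authority to halt the trial if any injuries or risks are identified based on interim findings".
- **Audits** has a DMC inspector verify incoming data every 3 months and check each electronic case report form for completion.
- **Training and calibration** makes one researcher responsible for "collecting clinical data, patient testimonials, and information on complications". It does not say how that information travels to the DMC.
- **Challenges and limitations** names haematoma and oedema as possible with the osteotomy, and adds: "It is also possible to create a depression in the sub-nasal area due to excessive removal of the ANS". According to the Intervention section, the ANS is removed only in the test group.

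**The concern.** The Harms rule is the only sentence in the article that ties a notice to the DMC to the occurrence of an event. Its wording requires two things at once: a surgical failure, and an unanticipated side effect or major adverse event. The same section says that failure has minimal probability, so the rule depends on something the authors hardly expect to happen.

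The Data monitoring section has no such condition. It gives the DMC adverse events to oversee and the authority to stop for any injury or risk. That authority is useful only if the facts arrive in time, and the Harms rule as written does not ensure this. What is at stake is how soon the DMC hears of a serious event after an otherwise uneventful operation, while further patients may be going to surgery.

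The opening assurance in Harms adds to the problem. It states as certain that no significant injury will occur, although another section of the same article acknowledges risks, one of them tied to the test procedure.

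**Working it through.** The plan states no figure on this point, so there is none to reproduce. The check compares the sections and looks at the timing they imply.

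**1. What the rule covers.** Let F be a surgical failure and E an unanticipated side effect or major adverse event. The Harms rule is F and E.

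| Situation | Notice under Harms as written | Within the remit in Data monitoring |
|---|---|---|
| F and E | yes | yes |
| E without F | no | yes, as an adverse event |
| F without E | no | yes, if it is an injury or a risk |
| neither | nothing to notify | nothing to oversee |

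The rule covers one of the three situations that could call for notice. With *or* in place of *together with* it covers all three.

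**2. Whether another parsing rescues it.** The sentence could be bracketed as (failure together with unanticipated side effects) or (major adverse events). A major event alone would then qualify. An unanticipated side effect alone and a failure alone would still not. The gap narrows but stays open.

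**3. What the other routes provide.** Inputs: auditor meetings every 2 months (Data monitoring), inspections every 3 months (Audits), follow-up of 3 months after surgery (Intervention), recruitment to 31 December 2023 and completion by 1 April 2024 (Trial status).

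- An event just after an auditor meeting waits up to 2 months for the next. If events fall evenly between meetings, the mean wait is 2/2 = 1 month.
- For the inspection alone, the longest wait is 3 months and the mean 3/2 = 1.5 months.
- Follow-up (3 months) is longer than the interval between meetings (2 months), so at least one meeting falls within each patient's follow-up if the schedule is kept. An event is therefore likely to have some occasion to be raised.
- The last patients have about 3 months between the close of recruitment and completion. A wait of 2 months would use 2/3 of that.

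These waits assume that adverse events are put to the auditor or inspector. The article describes the meetings as covering progress and an initial analysis, and the inspection as a check of data and form completion. It does not say that individual events are raised there. The article gives no start date for recruitment, so the number of operations that would take place during such a wait cannot be worked out.

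**4. The assurance on injury.** Harms excludes significant injury in advance. Challenges and limitations lists haematoma, oedema and a sub-nasal depression as possible, but does not call any of them significant. The two statements do not strictly contradict each other: one is an unsupported certainty and the other an acknowledged risk.

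**The case against.** The strongest reply is that the two sections describe two tiers. Data monitoring gives the DMC general oversight of adverse events, served by the 2-monthly meetings and 3-monthly inspections. Harms then adds prompt notice for the gravest combination. On that reading nothing conflicts. The English is also rough, and *together with* may be a loose rendering of *or*.

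Part of this stands. A reader might infer that the Harms rule is the DMC's only source of information and that it would therefore never receive most events. The documents do not support that, because Data monitoring and Audits both provide periodic routes and a researcher collects complications.

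A reader might also infer that complications will not be counted by arm. That is not supported either. The article is condensed, no analysis plan or case report form is shown, and such tabulation is commonly left to those documents. Nor does the assurance on injury set any procedure: the same section goes on to provide for things going wrong and for major adverse events.

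What the reply does not remove is the literal content of the rule. Even as an upper tier, it leaves a major adverse event without surgical failure to the next scheduled contact, and the article nowhere says that this is intended. If *or* was meant, the text should say *or*, since staff will follow the rule as printed.

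**Conclusion.** The point holds as an inconsistency between Harms and Data monitoring. The one explicit event-notification rule is conjunctive and covers one of three relevant situations, while the DMC's remit and its authority to halt carry no such condition. The consequence is missing or delayed event-driven notice. If the auditor meetings carry adverse events, the delay is at most 2 months; if only the inspection does, at most 3 months.

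This rests on reading the sentence as printed and on no unseen full protocol overriding it. No sample size, power or type I error is involved, and neither trial outcome is affected. The assurance on injury is a secondary matter of over-confident wording. It does not show that the protocol contradicts itself on risk.

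**What to change.** Reconcile Harms with Data monitoring. In the notification sentence, replace *together with* by *or*, so that any surgical failure, or any unanticipated or major adverse event, is notified to the DMC. Correct the garbled timing words in the same sentence. If the authors do intend two tiers, they should say so and state by which route the remaining events reach the DMC.

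Soften the opening assurance in Harms to an expectation that agrees with the risks acknowledged under Challenges and limitations.

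The cost is a change to two sentences, passed on to the surgical team and to the researcher who collects complications. It needs no extra patient, visit or radiograph. The DMC may receive somewhat more notices, which should be manageable in a trial of 26 patients.

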### Audits

The DMC will have an inspector verify the incoming data every 3 months, independent of the investigators. Each electronic case report form will be checked by the inspector for completion.

## Discussion

Achieving facial harmony through the correction of dentofacial anomalies requires careful and efficient planning and execution of orthognathic surgery. It is crucial to recognize that each action taken to achieve proper dental occlusion has an impact on the surrounding soft tissue. The primary aim of orthognathic surgery is to enhance both facial and dental aesthetics. This is achieved through a combination of orthodontic and surgical interventions to address facial deformities. For a majority of patients, the key driving factor behind seeking this treatment is the desire for improved soft tissue appearance [11]. First, we have to accurately predict the effects of each step on the soft tissue, particularly in the nasolabial region, and then plan the surgical approach accordingly [15]. Orthognathic surgery is performed to correct dentofacial deformities and enhance the functional relationship between the upper and lower jaws, leading to improved facial harmony. One common procedure used for this purpose is LeFort I osteotomy, which involves repositioning the maxilla in all three spatial planes to address various deformities. In this particular study, LeFort I osteotomy is utilized to achieve maxillary advancement in patients with class III deformities [3, 17]. Maxillary superior repositioning and advancement during orthognathic surgery can result in changes to the nasal tip position and the width of the nose as well as an upward rotation of the nasal tip and augmentation of the alar base. These changes are observed regardless of the extent of maxillary advancement or anterior/posterior impaction. One possible explanation for these alterations is that the repositioning of the anterior nasal spine and the dissection of soft tissues during surgery can lead to a partial loss of the original nasal measurements, resulting in subtle distortions [3].

In the present study, we will assess soft tissue changes in the middle and lower third of the face in a group of twenty-six non-growing patients with class III malocclusion. Cephalometric radiographs will be used to measure linear and angular parameters, allowing us to evaluate the alterations in soft tissue following maxillary advancement. It is worth noting that a study conducted by Nagori et al. in 2017 reported a reduction in nasal prominence after maxillary advancement, which contradicts the findings of other studies on the subject [11]. This randomized clinical research aims to investigate the impact of reducing the anterior nasal spine (ANS) on nasal profile changes following orthognathic surgeries that require a 3–5-mm advancement of the maxilla. The study will evaluate both objective data and patient-reported outcomes to provide valuable insights into the effects of ANS reduction on the aesthetic outcomes of orthognathic surgery. The findings of this research will be beneficial in guiding treatment decisions for patients who are considering orthognathic surgery, offering alternative options based on the expected nasal profile changes.

